## Abstract

**Clinical trial registration:**

ClinicalTrials.gov: NCT06468176; ID-RCB: 2023-A02376-39.

## 1 Introduction

Although rare, grade 2 and 3 diffuse gliomas, also called lower-grade gliomas (LrGGs) in the 2021 World Health Organization (WHO) classification (Louis et al., 2021), are the most common malignant brain tumor (Low et al., 2022). They are characterized by continuous tumor growth and a median age at diagnosis of 38 years for grade 2, and ~50 years for grade 3 (49 years for anaplastic oligodendroglioma and 52 years for anaplastic astrocytoma) (Ostrom et al., 2023). Overall survival ranges from 5 to 20 years, depending on different factors including histomolecular subtype, tumor volume at diagnosis, resection extent, and tumor growth rate (Ng et al., 2024). Currently, LrGG management remains palliative even for grade 2 tumors that are associated with better overall survival but will ultimately progress (Ng et al., 2024). In this context, one of the main goals is to ensure an acceptable health-related quality of life (HRQoL).

Due to the invasive nature of the disease and the treatment burden, LrGG is often associated with physical problems (e.g., epilepsy) and mental disorders. Psychological distress may gradually decrease over time; however, it remains a frequent complaint. It concerns ~56% of patients before surgery and persists in up to 40% of patients at month 6 after surgery (Rooney et al., 2011; Singer et al., 2018). Long-term studies suggest that such symptoms may continue well beyond the acute treatment phase. For instance, Boele and colleagues reported that 26 years after diagnosis, 23% of patients with LrGG still experienced depression and 53.3% persistent fatigue (Boele et al., 2023). Importantly, adherence to treatment and HRQoL are higher in patients with fewer psychological problems and this may improve their survival outcomes (Mainio et al., 2006). Among the available treatments, cognitive behavioral therapy (CBT) is an evidence-based non-pharmacological intervention (Barlow et al., 2017, 2020; Cuijpers et al., 2025). Few studies have investigated CBT effect on distress and HRQoL in patients with glioma. They demonstrated that comprehensive care based on the CBT principles can alleviate negative psychological states and improve HRQoL (Zhao and Xu, 2021; Boele and Klein, 2018; Liu et al., 2025). Therefore, CBT principles should be integrated in the management of patients with LrGG.

Neurocognitive impairment also is common in patients with LrGG (van Kessel et al., 2017; Schei et al., 2022; Reuvers et al., 2025). It can be observed already at diagnosis, and may, in some cases, lead to the incidental discovery of such tumors (Cochereau et al., 2016). After surgery, clinicians and patients regularly report impairment in one or more cognitive domains (Duffau, 2021). A study found that neurocognitive functioning was stable or improved in 82.8% of long-term survivors with LrGG at 7, 13 and 26 years after diagnosis (Boele et al., 2023). Neurocognitive disorders can significantly disrupt various aspects of the patients' lives, including schooling, employment, return-to-work, family life, and autonomy (Reuvers et al., 2025; Ng et al., 2020; Duffau, 2025; Duffau et al., 2025). In a recent study on 25 patients with grade 2 glioma planned for first-line chemotherapy after their last neurosurgery (median interval = 36 months) (Darlix et al., 2024), 40–53% reported cognitive complaints, using the European Organization for Research and Treatment of Cancer Core 30 (EORTC QLQ-C30) Cognitive Functioning subscale (Aaronson et al., 1993) and the Perceived Cognitive Impairment (PCI) score of the Functional Assessment of Cancer Therapy-Cognitive (FACT-Cog) questionnaire (Lange et al., 2016).

Neurocognitive rehabilitation is effective in several neurological conditions and in different primary cancers. (Bray et al. 2017) assessed a web-based cognitive rehabilitation program (*Insight*) in patients with cancer (excluding brain tumors) and self-reported cognitive symptoms. They found that the FACT-Cog PCI score was significantly improved in the intervention group (compared with the standard care group) at the end of the 15-week intervention, as well as HRQoL outcomes after 6 months. Few already finished or ongoing (NCT03948490) randomized trials focused on LrGG. The randomized trial by (Gehring et al. 2009) showed the promising effect of a face-to-face neuropsychological rehabilitation program on subjective cognitive complaints and objective neurocognitive deficits in 146 patients with “clinically stable” grade 2 glioma (i.e., without any evidence of disease progression for a minimum of 6 months before study entry). However, the implementation of this promising approach is limited by the lack of onco-neuro-psychologists (i.e., neuro-psychologists trained in oncology) (Manso-Ortega et al., 2022). To address this issue, some studies explored the use of digital neurocognitive telerehabilitation programs (van der Linden et al., 2018). Importantly, digital interventions on their own must be proposed at the right time (e.g., relative to treatments, symptoms), and cannot fully replace face-to-face rehabilitation led by a clinical neuropsychologist (van der Linden et al., 2021). Lastly, the other few clinical trials on neuropsychological rehabilitation in LrGGs have several limitations, such as small sample size (van der Linden et al., 2021; Locke et al., 2008; Richard et al., 2019; Yang et al., 2014; Maschio et al., 2015), heterogeneous populations (van der Linden et al., 2021; Yang et al., 2014; Zucchella et al., 2013), and/or methodological weakness (Maschio et al., 2015; Hassler et al., 2010; Miotto et al., 2014).

The aim of this French multicenter randomized study is to evaluate the impact of a hybrid neuropsychological rehabilitation program, which combines CBT delivered by a trained onco-neuro-psychologist with a digital neurocognitive training tool, in patients with LrGG and cognitive complaints during the post-therapy period.

## 2 Methods and analysis

### 2.1 Study design and settings

The FREEDOME study (*E*ff*icacité d'un programme mixte de*
ré*habilitation n*e*uropsychologique en*
d*istanciel chez*
d*es patients porteurs d'un gli*ome
*diffus de grade 2 ou 3: essai randomisé contrôlé*, Efficacy of a hybrid neuropsychological telerehabilitation intervention on cognitive complaints in patients with LrGG after therapy) (NCT06468176) is an ongoing, prospective, open-label, multicenter, randomized controlled trial carried out in France. Patient recruitment is open since June 2024. The study is expected to last 42 months in total: 24-month enrollment period and 18-month follow-up phase. Patient will be included through a two-step process that includes screening and inclusion visits. Eligible patients who consent to participate will sign a written informed consent (Supplementary material) before enrollment. Patients will be randomly allocated to the control arm (standard care) or the intervention arm (FREEDOME program) (1:2 ratio). Figure 1 shows the study timeline and Figure 2 the study flowchart. Table 1 presents the data collection schedule. This study follows the Standard Protocol Items: Recommendations for Interventional Trials (SPIRIT) checklist to ensure the quality of the study protocol.

**Figure 1 F1:**
[figure not shown]
The FREEDOME study timeline. ^1^Follow-up periods: month (M) 4, 6, 12, and 18 after inclusion (±2 weeks). ^2^Cognitive behavioral therapy by telehealth sessions (at least three sessions, maximum one session/week) and BrainHQ digital program (4 × 40-min session/week). ^3^Assessment of cognitive complaints, psychopathological functioning, patient's quality of life, fatigue, and neurocognitive functioning. ^4^Assessment of cognitive complaints, psychopathological functioning, patient's quality of life, and fatigue. D, day; FU, follow-up, EOI, end of intervention; EOS, end of study.

**Figure 2 F2:**
[figure not shown]
Flow diagram of the study FREEDOME. ^1^Expected number of patients. ^2^Chemotherapy or radiotherapy. ^3^Performed by a trained onco-neuro-psychologist (max 1 session/week for 15 weeks). ^4^Four-month program (Insight from Posit Science BrainHQ, San Francisco, California, 357 USA). FACT-Cog, Functional Assessment of Cancer Therapy-Cognitive Scale; PCI, Perceived Cognitive Impairment sub-score; HADS, Hospital Anxiety and Depression Scale.

**Table 1 T1:** Detailed data collection schedule.

**Data collected**	**Screening inclusion**	**Intervention**	**EOI visit (T1)**	**FU visit (T1^′^)**	**FU visit (T2)**	**EOS visit (T2^′^)**
	**D**_−15_ **to D**_−1_	**W1–15**	**M4** ±**2W**	**M6** ±**2W**	**M12** ±**2W**	**M18** ±**2W**
Eligibility criteria	✓					
Consent form signature	✓					
Randomization	✓					
Cognitive complaints (patient- ± caregiver-rated FACT-Cog, PRMQ)	✓		✓	✓	✓	✓
Psychological functioning (patient- ± caregiver-rated HADS, BDI-II, STAI-Y, BITe)	✓		✓	✓	✓	✓
Quality of life (EORTC QLQ-C30, BN20)	✓		✓	✓	✓	✓
Fatigue (MFI-20, ISI)	✓		✓	✓	✓	✓
Neurocognitive functioning (MoCA, WAIS-IV subtests, HVLT, SENTB, RMET)	✓		✓		✓	
CBT by videoconference (at least 3 sessions, maximum 1 session/week)		✓^a^				
BrainHQ program (4 × 40-min session/week)		✓^a^				

BDI-II, Beck Depression Inventory-II; BITe, Brief Irritability Test; CBT, Cognitive Behavioral Therapy; EORTC QLQ-C30 and BN20, European Organization for Research and Treatment of Cancer Core 30 and Brain-20; FACT-Cog, Functional Assessment of Cancer Therapy-Cognitive questionnaire; HADS, Hospital Anxiety and Depression Scale; HVLT, Hopkins Verbal Learning Test; ISI, Insomnia Severity Index; MoCA, Montreal Cognitive Assessment; PRMQ, Prospective and Retrospective Memory Questionnaire; RMET, Reading the Mind in the Eyes Test; SENTB, Standard Executive Neuropsychological Test Battery; STAI-Y, State-Trait Anxiety Inventory-Y; WAIS-IV, Wechsler Adult Intelligence Scale, Fourth Edition, subtests Coding and Symbol Search.

D, day; W, week; FU, follow-up, EOI, end of intervention, EOS, end of study.

^a^Experimental group only.

### 2.2 Study objectives

The primary objective is to assess the impact of the FREEDOME program on the perceived cognitive impairment in patients with LrGG at month 4 (M4) after the intervention. Secondary objectives include assessing the patient adherence, and evaluating the intervention effect on subjective cognitive and memory complaints, HRQoL (particularly, sleep, fatigue, return-to-work) and psychological problems at M4, M6, M12 and M18 after the intervention. The study will also assess neurocognitive functioning at baseline, M4 and M12, and investigate the relationship between subjective and objective cognitive outcomes. Lastly, exploratory objectives will focus on evaluating the longitudinal impact of the intervention on memory and irritability as perceived by family caregivers at M4, M6, M12, and M18.

### 2.3 Endpoint measures

The primary endpoint is the perceived cognitive impairment, assessed using the FACT-Cog PCI score (Lange et al., 2016) at M4. The self-report FACT-Cog questionnaire is used to assess subjective cognitive complaints and has been validated in patients with cancer. It also evaluates the cognitive impairment effect on HRQoL. It has a good internal consistency reliability (Cronbach's alpha between 0.74 and 0.91) and good convergent validity (significant correlations with the scores of scales assessing anxiety and depression).

Secondary endpoint measures will include:

Patient adherence (i.e., completing at least 25 h of the recommended 40 h of the digital program and attending three telehealth consultations). The 25-h threshold is based on the study by (Bray et al. 2017), where the FACT-Cog PCI score change was higher in participants who trained >25 h than in those who trained <25 h (16.3 vs. 12.6 points). The three telehealth sessions (at the intervention start, mid-point, and end) will ensure sufficient therapeutic support, address barriers, and will allow reviewing progress and delivering personalized recommendations.Comparison of the FACT-Cog PCI scores (Lange et al., 2016) at baseline, M6, M12, and M18.Comparison of the scores the three other FACT-Cog subscales at baseline, M4, M6, M12, and M18.Comparison of the Prospective and Retrospective Memory Questionnaire (PRMQ) scores (Guerdoux-Ninot et al., 2019) at baseline, M4, M6, M12, and M18.Comparison of the EORTC QLQ-C30 scores (Aaronson et al., 1993) and its module Brain-20 (BN20) scores (Taphoorn et al., 2010) at baseline, M4, M6, M12, and M18.Comparison of the 20-item Multidimensional Fatigue Inventory (MFI-20) (Gentile et al., 2003) and the Insomnia Severity Index (ISI) (Savard et al., 2005) scores at baseline and M4, M6, M12, and M18.Proportion of patients returning to work or increasing their work hours at M4, M6, M12, and M18.Changes in self-rated psychological distress, depression, anxiety and irritability between baseline and M4, M6, M12, and M18 using the Hospital Anxiety and Depression Scale (HADS) (Razavi et al., 1990), Beck Depression Inventory-II (BDI-II) (Beck et al., 1996), State-Trait Anxiety Inventory-Y (STAI-Y) (Bellaert et al., 2022), and Brief Irritability Test (BITe) (Bellaert et al., 2022), respectively.Differences (between baseline and M4 and M12) in the clinician-rated scores of the following neurocognitive tests: Montreal Cognitive Assessment (MoCA) (Nasreddine and Patel, 2016), Working Memory Index [score derived from the Digit Span and Arithmetic subtests of the Wechsler Adult Intelligence Scale, Fourth Edition (WAIS-IV)], Processing Speed Index (from the Coding and Symbol Search subtests of the WAIS-IV) (Wechsler, 2011), Hopkins Verbal Learning Test (global scores) (Rieu et al., 2006), Standard Executive Neuropsychological Test Battery (Bayard et al., 2023) (including the modified Stroop Delis-Kaplan test, the Digit Span subtest of the WAIS-IV, the Verbal Fluency Test, the Trail Making Tests A and B), and Reading the Mind in the Eyes Test (Prevost et al., 2014).Correlations between the FACT-Cog sub-scores or PRMQ scores and key neurocognitive domains (global functioning, executive functions, language, working memory, processing speed, and social cognition) at baseline, M4, and M12.

Exploratory secondary endpoints will include:

Family caregiver-rated PRMQ scores at M4, M6, M12, and M18 (Guerdoux-Ninot et al., 2019).Family caregiver-rated BITe scores at baseline and M4, M6, M12, and M18 (Bellaert et al., 2022).

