### 2.8 FREEDOME program

#### 2.8.1 Cognitive behavioral therapy

CBT sessions will be conducted remotely (telehealth sessions) by the same trained onco-neuro-psychologist with expertise in CBT at all centers to ensure consistency. Each patient will be offered at least three CBT sessions (maximum one per week over 15 weeks) to address cognitive psychopathology, emotional regulation, fatigue and sleep management, and give support for the digital cognitive rehabilitation program. The aim is to improve the patients' perception and interpretation of situations, fostering adaptive cognitive, emotional, and behavioral responses. During these sessions, the onco-neuro-psychologist will propose to assess cognitive distortions and individual cognitive profiles, followed by the development of strategies to increase emotional awareness, improve tolerance, enhance control, and foster adaptive coping behaviors.

Besides the digital program support, the telehealth sessions will focus on key determinants of fatigue and sleep. Fatigue and insomnia are very frequently reported by patients with cancer, and could have important psychosocial and emotional consequences, such as reducing daily activities and HRQoL (Baussard et al., 2022; Morin et al., 2006). In these sessions, factors such as cancer-related adjustments, fear of tumor progression, dysfunctional fatigue-related cognition, and negative social interactions will be discussed. If needed, the intervention will incorporate insomnia treatment components, such as sleep hygiene and sleep restriction, as developed in on-line insomnia-CBT interventions (Boinon et al., 2021, 2024).

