This approach may allow us to address both transdiagnostic emotional symptoms and specific issues encountered by patients with LrGG. Sessions will be standardized at all centers, with a minimum of three consultations and flexibility for additional sessions (up to one per week) for 4 months, depending on the patient's clinical profile. Tables 2, 3 present the CBT syllabus (overview and long version, respectively) for transparency and reproducibility.

**Table 2 T2:** CBT syllabus (overview).

**Session(s)**	**Core content**	**Theoretical framework**	**Clinical objectives**
Introductory session (mandatory)	Symptom review, therapeutic rationale, motivational enhancement, functional analysis (cognition, fatigue, sleep, emotional distress)	Unified Protocol (Barlow), CBT model of psychopathology	Build therapeutic alliance, clarify treatment goals, enhance motivation
Core sessions (≥2 mandatory; additional weekly sessions for up to 15 weeks, if clinically indicated)	Psychoeducation on emotions; assessment of cognitive distortions; cognitive restructuring; behavioral activation; fatigue- and sleep-focused strategies (CBT-I components: sleep hygiene, stimulus control, sleep restriction if needed); adaptive coping skills training	Unified Protocol (psychoeducation, cognitive restructuring, emotion regulation); CBT-I (as indicated)	Increase emotional awareness, challenge maladaptive cognitions, improve sleep/fatigue management, foster adaptive coping
Final/closure session (mandatory)	Relapse prevention, consolidation of the learned skills, recommendations for daily life and digital tool use	Unified Protocol (relapse prevention), CBT-I (maintenance)	Consolidate adaptive responses, enhance autonomy, reduce relapse risk

**Table 3 T3:** CBT syllabus (details).

**Module**	**Main objectives**	**Content/Techniques**	**Adaptations to LrGG**
1. Introduction and motivation	Assess symptoms and expectations; build alliance; enhance motivation	Motivational interviewing; goal setting; program overview	Link to cancer history and treatment experience
2. Psychoeducation on emotions	Understand adaptive role of emotions; differentiate normal vs. pathological responses	Psychoeducation; thought–emotion–behavior cycle	Applied examples: fear of progression, fatigue, irritability
3. Emotional awareness	Increase attention to emotional experience; reduce avoidance	Emotion observation; emotion journal	Adapted to cognitive limitations or impairments (guidance, visual aids)

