#### 2.8.2 BrainHQ digital application

The Brain HQ digital application (Insight from Posit Science Brain HQ, San Francisco, California, USA) is a digital neurocognitive training program designed based on the principles of neuroplasticity. It was developed by an international team of neuroscientists led by [name] with the objective of improving cognitive functions through structured exercises. Participants will train for 60–160 min per week, divided into 1–4 sessions of 40–60 min/each. The recommended training regimen consists of four 40-min sessions per week for 15 weeks (total = 40 h). A detailed overview of the exercises included in the application is provided in Table 4.

**Table 4 T4:** Detailed description of the BrainHQ digital program.

**Exercise**	**Content**
Double decision	This module leverages a unique, proven technology designed to accelerate processing speed and expand the useful field of vision. Commonly referred to as “speed training” in research, this technology has been used in many studies that demonstrate benefits such as faster visual processing, broader field of view, enhanced driving safety, and more.
Follow the target	Participants are required to divide their visual attention and track multiple moving objects simultaneously. The target tracker is designed to encourage patients to divide their focus by challenging them to follow several objects that move at the same time on the screen.
Visual scanning	This module trains patients to identify without effort specific visual patterns at high speeds, enhancing their overall visual acuity. The key skill targeted by this module is visual processing speed. During the exercise, the color, direction, and thickness of the scanning bars will vary to challenge the participants.
Attention to detail	Designed to improve patients' ability to make quick, precise saccades, this module trains the ability to notice subtle details with each eye movement. It focuses on quickly and reliably extracting information from each visual fixation.
Hawk eye	This module enhances visual accuracy, enabling patients to see details rapidly and precisely. This improves memory encoding, allowing patients to better retain the information they encounter (e.g., from a film, a wedding, house hunting, birdwatching). The ability to remember these details accurately helps them to discuss these experiences effectively in the future. The aim of this module is to improve everyday life activities.

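### Table 2 makes at least four CBT sessions mandatory, but the adherence endpoint and the rest of the article use three, so a patient can count as adherent after missing a mandatory session

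*Protocol article*

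**What the plan says.** Section 2.3 (Endpoint measures) lists patient adherence first among the secondary endpoints and defines it as "completing at least 25 h of the recommended 40 h of the digital program and attending three telehealth consultations". It then explains the session count: "The three telehealth sessions (at the intervention start, mid-point, and end) will ensure sufficient therapeutic support".

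Section 2.8.1 gives the same number twice in its text: "Each patient will be offered at least three CBT sessions (maximum one per week over 15 weeks" and, just before Table 2, "Sessions will be standardized at all centers, with a minimum of three consultations and flexibility for additional sessions". Table 1 and the legend of Figure 1 also give a minimum of three.

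Table 2, the overview of the CBT syllabus in the same section, has three separate rows: "Introductory session (mandatory"), then "Core sessions (≥2 mandatory; additional weekly sessions for up to 15 weeks, if clinically indicated"), then "Final/closure session (mandatory"). Each row has its own content and clinical objectives.

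On the digital component, section 2.8.2 says: "Participants will train for 60–160 min per week, divided into 1–4 sessions of 40–60 min/each". It recommends four 40-min sessions per week for 15 weeks, 40 h in total. Section 2.13 will report adherence rates with 95% confidence intervals. Section 2.12 says that a senior clinician supervises adherence to the manualized syllabus, and that session exposure and digital engagement are recorded.

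**The concern.** The article describes the minimum CBT course in two ways. Read row by row, Table 2 requires more sessions than the endpoint asks for. The endpoint and the syllabus can then disagree about the same patient: adherent by section 2.3, short of a mandatory session by Table 2.

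This matters because adherence is a named secondary objective (section 2.2). The Discussion also relies on adherence monitoring to show whether the digital tool is usable in patients with lower-grade glioma. If the adherence rate is meant to show how many patients received the program as described, its session component should match the program as described.

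**Working it through.** **Sessions.**

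| Place | Minimum number of CBT sessions |
|---|---|
| Figure 1 legend | 3 |
| Table 1 | 3 |
| Section 2.3, adherence endpoint | 3 (start, mid-point, end) |
| Section 2.8.1, opening text | 3 |
| Section 2.8.1, sentence before Table 2 | 3 |
| Section 2.8.1, Table 2 | 1 introductory + at least 2 core + 1 closure = at least 4 |

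A patient with exactly three sessions has 3 of at least 4, so at least one mandatory session is missing whichever three were attended. If the start session is the introductory one and the end session the closure (an assumption that section 2.3 does not state), the mid-point session is the only core session, where Table 2 asks for at least two.

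Table 2 would sum to three only if the introductory or the closure session also counted as one of the two core sessions. Neither the table nor the surrounding text says so.

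**How far the adherence rate could move.** With 187 patients randomized 2:1, the intervention arm has about 187 × 2/3 = 124.7, say 125 patients. If all of them form the denominator (an assumption), each patient whose classification changes moves the rate by 1/125 = 0.8 percentage points. The article gives no expected distribution of session counts, so the number affected cannot be computed. It is the number with exactly three sessions and at least 25 h of training.

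**Training time.** Hours = minutes per week × 15 / 60.

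- Recommended regimen: 4 × 40 = 160 min/week, and 160 × 15 / 60 = 40 h. This reproduces the stated total.
- Lower end of the stated range: 60 × 15 / 60 = 15 h.
- Pace needed for the threshold: 25 × 60 / 15 = 100 min/week.
- Ends of the weekly range: one session of 60 min = 60 min; four sessions of 40 min = 160 min. Both stated ends reproduce.

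A steady pace of 60 to 99 min/week thus lies within the stated range and stays below 25 h over 15 weeks.

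**The case against.** The strongest reply on sessions is that the endpoint agrees with the program minimum in every place but one. Table 2 is the outlier, so this is an inconsistency between a table and the text. That is correct, and it rules out the stronger reading that the endpoint conflicts with the program as a whole. It does not remove the conflict: Table 2 is presented as the syllabus for transparency and reproducibility, and fidelity is supervised against the manualized syllabus.

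A reader might also infer that the training figures are wrong. The documents do not support this.

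- **Weekly range.** Multiplying the extremes of session number and length (1 × 40 and 4 × 60) gives 40–240 min, but the weekly total is itself stated as the bound, and both its ends arise from permitted combinations. The 4 × 40 min in Table 1 is the recommended regimen, at the top of that range.
- **25-h threshold.** It is set against the recommended 40 h and justified by a larger change in the primary score above 25 h than below it in the cited trial (16.3 vs. 12.6 points). A threshold for adherence may lie above the lowest expected use. Section 2.12 says that use is not constrained, so low use can be tolerated without counting as adherent.

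Nor does it follow that the adherence rate cannot be interpreted. The definition is explicit, usage is measured automatically, and section 2.13 specifies no adherence-based analysis of effect.

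**Conclusion.** The session conflict is real: at least four mandatory sessions in Table 2 against three everywhere else. It rests on reading the three rows of Table 2 as separate sessions, which is how the table is laid out. Its consequence is that the adherence rate, as defined, can include patients who missed at least one mandatory session of the syllabus. How many is unknown.

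The training-time figures contain no error. They need only a clarification that the part of the weekly range below 100 min does not reach the adherence threshold over 15 weeks.

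The point is limited to one secondary endpoint. The primary analysis populations (intention-to-treat, and patients with the primary score at baseline and M4) do not depend on adherence, so the primary comparison and the sample size stand. It is a modest inconsistency, worth correcting because an endpoint relies on the figure.

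**What to change.** 1. Reconcile Table 2 with Figure 1, Table 1, section 2.3 and the text of section 2.8.1 on the mandatory number of CBT sessions. The clinical team decides which number stands. If the introductory or closure session is meant to count as a core session, Table 2 should say so.
2. Align the session component of the adherence endpoint in section 2.3 with the reconciled number.
3. Add a sentence to section 2.8.2 saying that 60–160 min per week (15–40 h over 15 weeks) is a range of expected use, and that a pace below 100 min per week does not reach the 25-h adherence threshold. The threshold itself need not change.

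The cost is small: wording in the protocol and one endpoint definition. Session exposure and usage are already collected, so patients already enrolled can be classified under the reconciled definition by their session count. If the reconciliation changes what patients are required to attend, and not only the wording, the sponsor should check whether it is a substantial amendment needing ethics committee approval under section 4. The definition should be settled before the adherence data are examined.

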If both patient and family caregiver agree, the family caregiver will provide an estimation of the patient's irritability and memory errors in daily life, by filling in the QMRP and BITe questionnaires (paper or digital version) at the same timepoints.

CBT sessions will not be recorded; however, the intervention fidelity and standardization will be ensured through regular supervision by a senior clinician, who will monitor the adherence to the manualized syllabus. All sessions will be delivered by the same trained onco-neuro-psychologist at all centers, ensuring consistency. In the rare event of absence, a senior clinician trained in CBT, neuropsychology and oncology will conduct the session, following the manualized syllabus. These measures provide structured oversight and preserve the intervention fidelity throughout the study.

In addition, baseline characteristics, compliance to the intervention (e.g., intervention adherence, session exposure, digital engagement) and other potential confounding parameters, such as psychotropic and anti-seizure drugs, corticosteroids, tumor laterality and eloquence, seizure frequency, and time since last treatment, will be collected/recorded in the electronic case report form to detect possible confounding effects.

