- the FACT-Cog PCI scores will be compared between arms and time points using a similar method. A 5% significance threshold will be applied with adjustments for multiple comparisons to control the alpha risk using the Benjamini–Hochberg method (Benjamini and Hochberg, 1995). All exploratory analyses will be performed without adjustment.- Partial correlations between the FACT-Cog or PRMQ subscale score and key cognitive domains will be evaluated using Spearman or Kendall Tau correlation coefficients, adjusted for distress (HADS) and fatigue (MFI-20, ISI). Each neuropsychological threshold will be defined according to the test guideline and taking into account many variables, such as age, sex and/or socio-cultural level.- Other questionnaire scores will be compared between arms with the Student's *t*-test or Wilcoxon/Mann-Whitney rank-sum test. An ANOVA or ANCOVA model will be used to adjust for potential confounders.

Within each arm, score differences (HADS, PRMQ, BDI-II, STAI-Y, BITe, MFI-20, ISI, QLQ-C30, and BN20) between baseline and the subsequent timepoints will be assessed using the paired Student's *t* or Wilcoxon signed-rank test.

First, the mean score change over time will be graphically represented using the LOcally Estimated Scatterplot Smoothing method (LOESS).

Then, Linear Mixed Models (LMMs) may be used to model the score changes over time in function of the group. These LMMs will include random intercepts and slopes, assuming a linear trajectory over time. If necessary, more flexible LMMs (e.g., spline-based models) may be considered.

Although the open-label design may expose the study to attention and expectancy biases, particularly regarding self-reported outcomes, the data analysts involved in the primary outcome analysis will remain blinded to group allocation.

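### The exploratory caregiver-rated memory endpoint does not name its baseline, although the parallel irritability endpoint does and the schedule collects both

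*Protocol article*

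**What the plan says.** The objectives (section 2.2) describe the caregiver part of the study as "evaluating the longitudinal impact of the intervention on memory and irritability as perceived by family caregivers at M4, M6, M12, and M18". Section 2.3 turns this into two exploratory endpoints: "Family caregiver-rated PRMQ scores at M4, M6, M12, and M18" and "Family caregiver-rated BITe scores at baseline and M4, M6, M12, and M18". The patient-rated PRMQ, a secondary endpoint in the same section, is compared "at baseline, M4, M6, M12, and M18".

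Table 1 has a row labelled "Cognitive complaints (patient- ± caregiver-rated FACT-Cog, PRMQ", ticked at screening/inclusion and at M4, M6, M12 and M18. The row with BITe is ticked at the same five visits. Section 2.12 says that, where patient and caregiver both agree, the caregiver reports on memory errors and irritability "by filling in the QMRP and BITe questionnaires (paper or digital version) at the same timepoints".

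Section 2.13 compares the other questionnaire scores between arms with a t-test or rank-sum test, and allows an ANOVA or ANCOVA for potential confounders that it does not list. It also plans within-arm score differences, PRMQ and BITe included, "between baseline and the subsequent timepoints will be assessed using the paired Student's" t-test or signed-rank test. It does not say whether caregiver ratings are among these scores.

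**The concern.** Two caregiver scales, completed together by the same person, are given different sets of timepoints without a reason. The scale without a baseline is the memory scale, and the objective is to follow the effect on memory over time. Follow-up scores alone can show that the arms differ. They cannot show how far either arm has moved from its level before the intervention, and they do not use the strongest available predictor of the outcome.

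There is also a practical side. Recruitment has been open since June 2024 (section 2.1). A site working from the endpoint list instead of Table 1 could skip the caregiver PRMQ at inclusion, and a missed baseline cannot be recovered later. The article does not show that any site has done so.

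**Working it through.** **Timepoints side by side**

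| Place | Caregiver memory scale | Caregiver irritability scale |
|---|---|---|
| Section 2.2, objective | M4, M6, M12, M18 | M4, M6, M12, M18 |
| Section 2.3, endpoints | M4, M6, M12, M18 | baseline, M4, M6, M12, M18 |
| Table 1, schedule | inclusion, M4, M6, M12, M18 | inclusion, M4, M6, M12, M18 |
| Section 2.12, collection | same visits as the irritability scale | same visits as the memory scale |

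Only section 2.3 treats the two scales differently. Section 2.12 calls the memory questionnaire QMRP, which the article does not define. I read it as the PRMQ, because it covers memory errors and is paired with BITe.

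**Is the inclusion score a proper baseline?** Section 2.7 places randomisation after the inclusion assessment. A caregiver score taken at that visit therefore precedes allocation and can serve as an ANCOVA covariate.

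**What the baseline is worth.** The article gives no sample size, power or correlation for the caregiver endpoints, so there is no figure of its own to reproduce. Let r be the correlation between a caregiver's baseline and follow-up scores, assumed equal in both arms. Relative to comparing follow-up scores alone, the variance of the arm difference is multiplied by:

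- ANCOVA on baseline: 1 − r²
- simple change from baseline: 2 − 2r

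| r (assumed) | ANCOVA factor | Reduction | Equivalent sample, 1/(1 − r²) | Change-score factor |
|---|---|---|---|---|
| 0.3 | 1 − 0.09 = 0.91 | 9% | 1.10 | 1.4 |
| 0.5 | 1 − 0.25 = 0.75 | 25% | 1.33 | 1.0 |
| 0.7 | 1 − 0.49 = 0.51 | 49% | 1.96 | 0.6 |

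At r = 0.5 to 0.7 the adjusted analysis is worth 1.33 to 1.96 times as many caregivers. ANCOVA is the more precise use of the baseline at each of these values: a simple change score loses precision at r = 0.3, gains nothing at r = 0.5, and gains less than ANCOVA at r = 0.7. I give no power figure, because the article states neither how many caregivers are expected nor what effect is looked for.

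**The case against.** The strongest reply is that this is one word missing from one item in an exploratory list. The baseline is scheduled, and section 2.13 plans PRMQ differences from baseline, allows ANCOVA and mentions mixed models over time, without excluding caregiver ratings. Leaving baseline out of an endpoint's timepoints need not mean that it is ignored: the primary endpoint is written as the score at M4, yet its evaluable population requires both a baseline and an M4 score. The caregiver PRMQ item also matches the objective in section 2.2, so BITe could be called the odd one out. Finally, covariates for an exploratory outcome are commonly left to the analysis plan.

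Most of this stands. A reader might infer that the caregiver baseline will be discarded, or that no change can be shown; the article supports neither. What remains is that section 2.3 disagrees with Table 1 and section 2.12, and that the article itself states those timepoints.

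A reader might also infer that optional caregiver participation makes the arms unbalanced. The article does not support that either. If caregivers agree at inclusion, before allocation, the subset is still randomised. Self-selection then limits how far the result generalises, and larger chance imbalance comes only from the smaller number. Section 2.12 does not say when agreement is sought, so dependence on arm cannot be assumed.

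The Table 1 labels could be read as having caregivers rate FACT-Cog, HADS, BDI-II and STAI-Y. The text rules this out: section 2.3 treats these scales as completed by the patient, and sections 2.2, 2.3 and 2.12 confine caregivers to memory and irritability. The label is loose shorthand.

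**Conclusion.** The point holds as an inconsistency in the endpoint definition. The caregiver PRMQ endpoint does not name a baseline that Table 1 schedules, that section 2.12 implies, and that the parallel BITe endpoint includes. The follow-up comparison of arms is valid as it stands, and loss or non-use of the data is not shown.

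The gain from naming and using the baseline is one of precision and of being able to describe change: a 25% to 49% lower variance of the arm difference if r lies between 0.5 and 0.7, and about 9% if r is only 0.3. These correlations are assumptions, since the article gives none. The endpoint is exploratory and no power is claimed for it. Severity: nice to have.

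**What to change.** In section 2.3, give the caregiver-rated PRMQ the same five timepoints as the caregiver-rated BITe: baseline, M4, M6, M12 and M18. In section 2.13 or the analysis plan, state that the arms are compared on each caregiver scale by ANCOVA with that caregiver's own baseline score as covariate, and say whether the planned differences from baseline include caregiver ratings.

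As minor wording, attach the caregiver label in Table 1 to PRMQ and BITe only, and use one abbreviation for the memory questionnaire throughout.

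The cost is a few words and one covariate per model. No assessment is added where Table 1 is followed. A reminder to sites that the caregiver PRMQ is due at inclusion would guard against missed baselines among patients still to be enrolled.
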